## 2. Trial Design

Seventy patients will be enrolled in a Phase II randomized controlled trial. The study will be developed in two stages. In the first step, 28 patients will be enrolled: 14 of these will receive ECT for four weeks after neo-adjuvant treatment and then local excision (treatment group) and 14 patients will receive neo-adjuvant treatment and then local excision (control group). Electrochemotherapy will be performed with the CLINIPORATOR™ and an intravenous dose of Bleomycin. If an increase of response rate is observed in the first stage and/or feasibility/safety is demonstrated, the second stage of the trial will be performed. In the second step, an additional 42 patients will be enrolled and treated. Trial design flow-chart is showed in Figure 1.

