### 2.2. Subject Selection

Eligible patients will be randomly assigned (1:1) to the treatment group or the control group. The treatment group assignment will be assigned blindly and sequentially in the order in which eligible patients are enrolled in the study. Patients eligible for inclusion in the protocol (see Table 1) will be informed in detail about the study and, if they consent to participate, they will sign the informed consent form (Appendix A), witnessed by a member of the research group.

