### 2.8. Statistic Considerations

#### 2.8.1. Description of Sample Size Calculation and Planned Statistical Analyses

The sample size was determined by the Group-Sequential Superiority approach with a Margin Tests for the Difference of Two Proportions [36] using a complete response rate to the TRG after local excision as an endpoint. Sample size estimation has been carried out by using the superiority hypothesis in two independent parallel sample proportions [38,39,40,41,42]. According to the literature data, neoadjuvant chemo-radiotherapy treatment in LARC results in a complete response of 25% [43,44,45,46,47,48].

The proportion in the treatment group is assumed to be 0.25 under the null hypothesis and 0.50 under the alternative hypothesis. The proportion in the control group is assumed to be 0.25. The significance level of the one-sided test was targeted at 0.10 and the power at 80%.

An interim analysis will be conducted when 28 patients are enrolled (the percent of the sample size accumulated up to the corresponding look will be 40.0%). If a complete response rate to the TRG after local excision is noted in less than 25% of patients in the treatment group and/or feasibility/safety was not demonstrated, the study will be discontinued, otherwise a further 42 patients will be enrolled in the study.

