#### 2.8.3. Interim Analysis

Interim analyses will be fixed after the first step of the study. A conclusive analysis will be performed at the end of the treatment of patients enrolled in the second stage. If a complete response rate to the TRG after local excision is noted in less than 25% of patients in the treatment group, and/or feasibility/safety was not demonstrated, the study will be discontinued. A difference of 20% for both AE rate and surgical complications rate between the two arms will be considered significant enough to discontinue the trial.

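### The numeric interim efficacy rule tests the ECT arm alone against a fixed 25%, which conflicts with the protocol's own between-arm gate and screens poorly if the control response rate is well above 25%

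*Protocol article*

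**What the plan says.** Stage 1 is described in section 2: "In the first step, 28 patients will be enrolled: 14 of these will receive ECT", and the other 14 are controls. Section 2.2 confirms the allocation: "Eligible patients will be randomly assigned (1:1) to the treatment group or the control group".

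The gate to stage 2 is worded in two ways.

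- Section 2 (and the Abstract in near-identical terms): "If an increase of response rate is observed in the first stage and/or feasibility/safety is demonstrated, the second stage of the trial will be performed". No comparator is named there, but the last paragraph of the Discussion describes the outcome as a rise in complete response in the treatment group relative to the control group.
- Section 2.8.3, and section 2.8.1 in the same terms: "If a complete response rate to the TRG after local excision is noted in less than 25% of patients in the treatment group", or if feasibility/safety is not shown, the trial stops. Section 2.8.1 completes the rule: "the study will be discontinued, otherwise a further 42 patients will be enrolled in the study".

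The rest of the design is comparative. Section 2.8.1 states: "Sample size estimation has been carried out by using the superiority hypothesis in two independent parallel sample proportions". The final test in section 2.8.2 is a one-sided Fisher exact test between the arms at 0.10. The interim safety stop in section 2.8.3 also compares the arms: "A difference of 20% for both AE rate and surgical complications rate between the two arms will be considered significant enough to discontinue the trial".

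**The concern.** The efficacy part of the numeric rule has a single input, the number of TRG 1–2 responders among 14 ECT patients. The concurrent controls are randomised, excised and graded, yet do not enter it. A one-arm count cannot show an increase over control. A stage 1 result of 4/14 on ECT against 10/14 on control would pass.

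With a fixed one-arm cut-off, the chance of opening stage 2 under no effect is set by the background response rate. If that rate is higher than planned, stage 2 may open for an ECT arm that is no better, or worse, and 21 more patients would receive ECT (half of the 42) in a trial with little chance of success.

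**Working it through.** **Inputs.** From sections 2, 2.8.1 and 2.8.2: 14 per arm at the interim; 21 per arm in stage 2; 35 per arm in total; control rate 0.25; ECT rate 0.25 under the null and 0.50 under the alternative; one-sided 0.10; power 80%; final one-sided Fisher test. Safety stops are left out, so every figure below concerns the efficacy condition only.

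**The plan's own figures.** 28/70 = 40.0%, as stated. For 25% v 50%, the pooled normal formula gives, per arm,

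n = [1.2816·√(2·0.375·0.625) + 0.8416·√(0.25·0.75 + 0.5·0.5)]² / 0.25² = (0.877 + 0.557)² / 0.0625 ≈ 32.9, so 33.

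With 35 per arm the same approximation gives power 81.8%. So 70 patients at 80% is consistent with a between-arm comparison plus a small group-sequential allowance. That allowance is an assumption, because no boundary is given. Exact Fisher power at 35 per arm with no interim gate is 73.8%.

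**The rule as a count.** 3/14 = 21.4% is below 25%, and 4/14 = 28.6% is not. Stage 2 therefore opens if X ≥ 4, where X ~ Bin(14, ECT rate):

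P(open) = 1 − Σ(k=0..3) C(14,k) p^k (1−p)^(14−k).

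At p = 0.25 this is 1 − (0.018 + 0.083 + 0.180 + 0.240) = 0.479.

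**Comparison of rules.** Let Y be the control count, Y ~ Bin(14, control rate), independent of X. Three rules are compared: as written (X ≥ 4); between-arm only (X ≥ Y); combined (X ≥ 4 and X ≥ Y). For the combined rule, P(open) = P(X ≥ 4) − P(X ≥ 4 and X < Y). At 25/25 this is 0.479 − 0.076, about 40%.

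| True control rate | True ECT rate | Basis | Written | Between-arm only | Combined |
|---|---|---|---|---|---|
| 25% | 25% | protocol null | 48% | 59% | 40% |
| 25% | 20% | planned control, ECT assumed | 30% | 46% | 25% |
| 25% | 15% | planned control, ECT assumed | 15% | 33% | 12% |
| 30% | 30% | upper figure in the Discussion | 64% | 58% | 49% |
| 40% | 40% | assumed | 88% | 58% | 56% |
| 50% | 30% | assumed | 64% | 18% | 18% |
| 60% | 40% | assumed | 88% | 19% | 19% |
| 25% | 50% | protocol alternative | 97.1% | 94.5% | 93.2% |

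**Final error rates.** These sum, over all stage 1 results that pass the gate, the probability of that result times the probability that the 35 v 35 Fisher test gives p < 0.10.

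- Written rule: 0.052 at 25/25; power 72.8% at 25% v 50%.
- Between-arm rule alone: power 72.7%.
- Combined rule: power 72.0%.
- In the two assumed cases with ECT 20 points worse, final success under the written rule is below 0.1%.

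**The case against.** A minimum-activity floor in the experimental arm at stage 1, with a randomised comparison at the end, is a coherent phase II choice. Efficacy is still judged between arms by the final test, and type I error with this gate is below 0.10. That much stands. It does not explain why sections 2 and 2.8 describe the gate differently.

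Four stronger readings are tempting, and the documents do not support them.

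- A reader might infer that stage 2 would usually open even when ECT patients respond less often than controls. At the only planned control rate, 25%, a truly worse ECT arm opens stage 2 less than 48% of the time. With 25% in both arms, given that fewer ECT than control patients have responded, it opens 18.5% of the time. The rule passes a worse ECT arm in most trials only if the true ECT rate exceeds about 25.6%, so the control rate must be higher still.
- A reader might infer that the controls play no part in the interim. The safety stop compares the arms; only the numeric efficacy condition ignores them.
- A reader might infer a false-positive problem. There is none: the weakness is in futility screening.
- A reader might conclude that a between-arm comparison should replace the floor. At a 25% control rate that does worse: it opens 33% rather than 15% of the time when ECT is truly 15%. It also has no activity floor, so 0/14 v 0/14 would continue.

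The control rates of 40% to 60% are not in the protocol. The direction is plausible, because the 25% is cited for neoadjuvant chemo-radiotherapy in locally advanced disease generally (section 2.8.1). This trial enrols only confirmed major clinical responders (Table 1) and counts both TRG 1 and TRG 2 as response (sections 2.6 and 2.8.2). The size is not known.

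**Conclusion.** The inconsistency is in the text and rests on no assumption: the only numeric efficacy rule is one-arm, while the gate in section 2, read with the Discussion, and the sizing and final test are between-arm.

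Its practical size depends on the true control rate. Near 25% the rule screens acceptably against a worse ECT arm. Well above 25% it does not: with no effect it opens stage 2 in 64% of trials at 30% and 88% at 40%, and at assumed rates of control 50% v ECT 30% and control 60% v ECT 40% it opens 64% and 88%. The cost is continued enrolment with little prospect of success; there is no inflated type I error. The wording should be reconciled before the interim.

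**What to change.** Use one efficacy gate in the Abstract and sections 2, 2.8.1 and 2.8.3. Keep the 25% floor and add a between-arm condition, for example: *the efficacy condition fails if fewer than 25% of the first 14 ECT patients respond, or if fewer ECT than control patients have TRG 1–2.* The same edit should settle how efficacy and feasibility/safety combine, since section 2 joins them with and/or for continuing while section 2.8 does so for stopping. The safety criterion itself is not touched.

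The combined rule can never open stage 2 more often than the written one. It needs no extra patients or data. At 25% v 50%, early stopping rises from 2.9% to 6.8% and power falls from 72.8% to 72.0%.

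As worded, a tie passes, and strictly a tie is not an increase. If the sponsor wants a strict increase as well as the floor, stage 2 opens 88% of the time at 25% v 50%, so early stopping there is about 12%. The choice on ties should be stated.

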### 2.4. Duration of the Study and Follow up

The study will last 36 months with five follow-up years for all patients enrolled. The time for enrolment will be 36 months.

Patients after local excision will be visited every three months in the first two years, and then every six months in the following three years.

This study is subject to stopping rules. Patients can decide to interrupt the treatment. Subjects who discontinue/withdraw from study participation will be evaluated by study personnel.

Starting from the informed consent signature, any event occurring during the treatment phase and/or the follow up phase, will be considered an Adverse Event (AE) and will be recorded. Any clinical or biological abnormalities not present at the trial start will be considered intercurrent events.

The visits scheme is summarized in Table 2.

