#### 2.8.2. Statistical Analysis

The treatment feasibility/safety of surgery following electrochemotherapy will be assessed considering the number of participants with compromised surgery following electrochemotherapy assessed by the R1 resection rate, circumferential resection margin (CRM) involvement, non mesorectal resection plane, and post-operative complications according to the Clavien-Dindo Classification. A surgical complications rate of 30–40% was reported in the literature for conventional neoadjuvant treatment followed by TME [37]. The evaluation of each arm will be performed at Visit 5 (12 weeks from ECT/8 weeks from LE).

Complete response rate (TRG 1 and 2), disease recurrence rates and percentages will be compared among the two groups. A one-sided Fisher exact test will be performed to test the differences between the groups. Differences will be considered significant at *p* < 0.10. A Chi square test will be performed to assess statistically significant differences among the groups for the categorical variable.

The time interval between the recruitment date and local disease progression will be represented using the time of treatment failure and median and minimum–maximum values will be considered.

The scores obtained by the QOL, pain and satisfaction questionnaires will be evaluated. Any serious adverse events and their intensity, according to the NCI-CTCAE classification (version 5.0), will be registered in the first two days post-procedure.

Mean ± standard deviation will be considered for normally distributed continuous variables while the median and interquartile range (IQR) will be presented for non-normally distributed continuous variables.

For continuous variables, the difference between follow-up values and baseline values will be tested by a 2-sided Student t-test or by a Mann–Whitney test while, for the categorical variables, the McNemar test and the marginal homogeneity test will be use [49,50].

Time to event outcomes will be analyzed using the Kaplan–Meier method and survival curves will be compared using the log-rank test.

Mixed effect regression models will be used to analyze longitudinal data by adjusting for proper covariates.

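### The 20% safety stop at 14 patients per arm leaves open its direction, whether one or both criteria are needed, and the AE severity; the false-stop risk and the power depend on how it is read

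*Protocol article*

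**What the plan says.** The interim look is fixed in section 2.8.1: "An interim analysis will be conducted when 28 patients are enrolled". Section 2 splits these patients into two arms: "In the first step, 28 patients will be enrolled: 14 of these will receive ECT for four weeks after neo-adjuvant treatment", while "14 patients will receive neo-adjuvant treatment and then local excision (control group" are the controls. Section 2.2 confirms the ratio: "Eligible patients will be randomly assigned (1:1) to the treatment group or the control group".

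Section 2.8.3 makes failure on safety a reason to stop: "and/or feasibility/safety was not demonstrated, the study will be discontinued". It then gives the numeric criterion: "A difference of 20% for both AE rate and surgical complications rate between the two arms will be considered significant enough" to end the trial. No direction, test, interval, or absolute or relative scale is given.

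The two rates are described elsewhere. Section 2.4 defines events broadly: "any event occurring during the treatment phase and/or the follow up phase, will be considered an Adverse Event (AE", with no limit on grade or cause. Section 2.7 adds a collection at Visit 3, before excision, to isolate events due to ECT. It names CTCAE version 5.0 but sets no grade. Section 2.8.2 assesses surgical safety at Visit 5 and names Clavien-Dindo, again without a grade. The only rate offered is in section 2.8.2: "A surgical complications rate of 30–40% was reported in the literature for conventional neoadjuvant treatment followed by TME". No AE rate and no complication rate for local excision is given.

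The sample size in section 2.8.1 uses TRG complete response as its only endpoint: 0.25 versus 0.50, one-sided 0.10, power 80%.

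**The concern.** This rule decides whether 42 more patients are enrolled, and feasibility/safety is a primary endpoint (section 2.1.1). Because section 2.8.3 fixes a number, the issue is a stated rule that cannot be applied in one way only, not a detail left for an analysis plan.

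The words *for both* can mean that the threshold applies to each rate separately, or that both must be exceeded together. A raw 20-point gap in 14 versus 14 patients is within ordinary chance variation, so the first reading can end a trial of a safe treatment. The second reading rarely does so but can let real harm pass. Only the ECT arm receives bleomycin, electric pulses and the accompanying anaesthesia before Visit 3 (section 2.3.2). Without a severity level, minor events could therefore count towards the stop. The 80% power takes no account of a stop that is worded as mandatory.

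**Working it through.** **1. The plan's own sample size.** Inputs from section 2.8.1: 0.25 versus 0.50, one-sided 0.10, power 80%, one look at 28/70 = 40%. The spending function is not stated. Assuming an O'Brien-Fleming type with pooled variance, 34 per arm gives power 0.799 and 35 per arm gives 0.808. So 70 patients is reproduced, on TRG response alone.

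**2. What 20% means at 14 per arm.** Read as an absolute difference, 2/14 = 14.3% does not reach it and 3/14 = 21.4% does. The trigger is a gap of 3 patients. One-sided Fisher p is 0.22 for 7 versus 4, and C(14,3)/C(28,3) = 364/3276 = 0.11 for 3 versus 0.

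**3. False stops with no true difference.** Let X_E and X_C be independent Binomial(14, p) counts in the ECT and control arms. For one criterion with ECT worse, f(p) = P(X_E − X_C ≥ 3), by exact enumeration. For two independent criteria at the same rate, either one stopping has probability 1 − (1 − f)², and both being needed has f². The rates are assumptions: 30–40% is the TME figure, and 10–20% allows for local excision having fewer complications.

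| True rate, both arms | One criterion | Either suffices | Both needed |
|---|---|---|---|
| 10% | 0.0545 | 0.106 | 0.003 |
| 20% | 0.1164 | 0.219 | 0.014 |
| 30% | 0.1504 | 0.278 | 0.023 |
| 40% | 0.1673 | 0.307 | 0.028 |

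If AE rates lie between 20% and 70% while complications are 10%, the *either* figure is 0.165–0.218 and the *both* figure 0.006–0.009. Perfect correlation at equal rates would raise the *both* column to the one-criterion column.

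**4. Detection of a true 20-point excess (30% versus 50%).** One criterion: 0.552. With the excess on both endpoints and independence, *both needed* gives 0.552² = 0.30 and *either suffices* gives 1 − (1 − 0.552)² = 0.80. Perfect correlation would bring the *both* figure up to 0.55.

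**5. Power.** Take the stated 80%, a stop applied mechanically, and safety independent of response: power ≈ 0.80 × (1 − false stop).

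- Either suffices, rates 30–40%: 0.80 × (1 − 0.278) = 0.58 to 0.80 × (1 − 0.307) = 0.55.
- Both needed, rates 30–40%: 0.80 × (1 − 0.023) = 0.78 to 0.80 × (1 − 0.028) = 0.78.
- At rates of 10%: 0.80 × (1 − 0.106) = 0.72 (either) and 0.80 × (1 − 0.003) = 0.80 (both).

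All of this assumes 14 evaluable patients per arm. The look is set at 28 enrolled, but surgical safety is read at Visit 5, so fewer may be evaluable at that moment.

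**The case against.** A reader might conclude that the rule would often stop a safe trial, whatever its meaning. The documents do not support that. If both criteria must be met with ECT worse, the false-stop probability is at most about 3% under independence and power barely moves.

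A reader might also infer that an excess in the control arm would stop the trial, since no direction is written. At rates of 30–40% that would give 30–33% false stops per criterion. The reading is strained. The 20% sentence follows the clause on safety not being demonstrated, and sections 2.1.1 and 2.8.2 make clear that the safety in question is that of ECT. The missing direction needs a wording correction, and the undirected figures should carry no weight.

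The AE criterion may look open-ended because of section 2.4. Sections 2.7 and 2.8.2 do supply windows (Visit 3 before excision, and Visit 5). What is missing is a link from section 2.8.3 to those windows, and a severity level. It is also tempting to claim that minor events in the ECT arm make a stop nearly certain. That needs AE rates which the documents do not give.

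The 30–40% complication rate is for TME, whereas both arms here have local excision first. That objection stands, and is why the range starts at 10%. Independence is also an assumption, since a surgical complication may be recorded as an AE too.

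Finally, safety stops are often left out of efficacy power. That is reasonable for a non-binding rule, but section 2.8.3 says the study will be discontinued. Section 2 words the go-ahead more loosely, with *and/or*, so the text does not settle how binding the stop is.

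**Conclusion.** The point holds in conditional form. Section 2.8.3 fixes a decision rule whose behaviour differs about tenfold or more between its two natural readings, and neither reading performs well.

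- **Either criterion suffices:** with ECT worse, a treatment with no true excess is stopped with probability 11–31% over rates of 10–40%. At rates of 30–40% this is about 3 trials in 10, and the stated 80% power becomes about 55–58%.
- **Both criteria are needed:** false stops are about 0.3–3% and power stays near 78% at rates of 30–40%. A true 30% versus 50% excess on both endpoints is missed about 70% of the time.

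Per criterion, the false-stop probability is 5–17% and detection 55%. These results rest on equal true rates that are assumed, 14 evaluable patients per arm, independent endpoints, safety independent of response, and a rule applied as written. Strong correlation would move the *both* reading towards the one-criterion figures.

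**What to change.** Reconcile sections 2.4, 2.7, 2.8.1, 2.8.2 and 2.8.3 before any interim counts by arm are seen:

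- State the criterion as the absolute difference ECT minus control, triggered only when ECT is worse.
- Tie each rate to the window already defined for it: Visit 3 before excision for ECT-related events, Visit 5 for surgical safety.
- State whether one criterion is enough or both are needed.
- Let the sponsor's safety reviewers set the severity level for AEs and complications, using the CTCAE and Clavien-Dindo grades already collected.
- Report false-stop and detection probabilities over a range of plausible rates, including low complication rates for local excision.
- Either restate power with the binding safety stop included, or declare the stop non-binding.

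The cost is revised wording, a short operating-characteristics table and, if the stop stays binding, a less favourable stated power. No new data are needed.

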## 3. Discussion

The efficiency and safety of ECT have been demonstrated in preclinical and clinical Phase I and I/II studies in patients with melanoma, head and neck squamous cell carcinoma, Merkel cell carcinomas, basal cell carcinoma and adenocarcinoma nodules. The efficacy of ECT has already been proven in skin tumors, and in mucosal and submucosal tissues with high tumor control. Recent studies have demonstrated the feasibility and safety of ECT in the treatment of deep tumors (locally advanced pancreatic cancer, hepatic colorectal metastases, cancerous thrombosis of the portal vein, cholangiocarcinoma hepatocellular carcinoma) [10,11,12,13,14,15,16,17,18,19,20,21,22,23,24,25,26]. In addition, ECT has been used as a neoadjuvant treatment for tumor downstaging before surgical treatment to increase the rate of conservative surgical interventions.

Moreover, colorectal cancer as well as gastric and esophageal tumors have been treated with endoluminal electrodes without adverse events or complications demonstrating a tumor regression (https://clinicaltrials.gov/ct2/show/NCT03040180, accessed on 10 April 2021) [27].

Currently, 45–55% of rectal cancer patients receive preoperative chemo-radiotherapy for LARC. TME is the gold standard in rectal cancer surgery and is comprised of resection of the rectum together with the fatty tissue surrounding the rectum [45]. For LARC, therapy consists of preoperative chemo-radiation therapy (pCRT) or radiotherapy alone followed by TME [51,52,53,54,55,56,57,58,59,60,61,62].

The high morbidity and functional complications associated with TME motivate the search for conservative treatments with sphincter preservation for patients with early rectal cancer at diagnosis and patients with significant tumor regression after pCRT, with the advantage of reducing morbidity and providing a “true” organ-sparing approach [42]. It has also been suggested that a prolongation of the treatment interval might improve overall survival [63,64,65].

Complete pathological response after neoadjuvant therapy in rectal cancer has been shown to be an independent predictor of overall survival and a decrease in local recurrences; up to 30% of patients will achieve a complete or near complete response [46,47,48].

The idea is to use electrochemotherapy in patients with LARC and major clinical response after neoadjuvant therapy, before surgery (local excision of the rectum as the surgical approach used in clinical practice) and assuming an increase in the local control of residual disease and of complete response rate, confirmed by histopathological examination using Tumor Regression Grade. The TRG is a powerful indicator of response to a neoadjuvant treatment in rectal cancer and can measure the effectiveness of neoadjuvant therapy.

ECT has been shown to have limited side effects, a high degree of patient acceptability and acceptable costs. Treatment is performed under local or general anesthesia and does not always require hospitalization. The outcome is to verify the feasibility/safety of electrochemotherapy in this indication and the increase of complete response rate in the treatment group with respect to control group.

